### 2.8. Data Analysis Strategy

#### 2.8.1. Quantitative Data

Quantitative data will be analyzed using IBM SPSS Statistics (version 28). The analysis and presentation of data will be in accordance with CONSORT guidelines, in particular the extension to feasibility and pilot trials [35].

Descriptive statistics will be computed to assess feasibility and acceptability. Fidelity data collected from the weekly review forms will be assessed based on a cumulative score across sessions, as well as a percentage of the maximum cumulative score. Standard descriptive statistics will be computed to report demographics, as well as baseline and outcome scores. An intention-to-treat (ITT) analysis approach will be employed to ensure the validity and generalizability of study findings by minimizing bias and providing a robust assessment of treatment effects [45]. Effectiveness analyses, using data from our psychological measures, will be performed with data from Parent 1, while data collected from Parent 2 will be examined independently to consolidate our findings. An analysis of covariance (ANCOVA) will be used to examine differences between intervention and waitlist control arms, taking pre-intervention data into account as a covariate. Cohen’s d effect sizes will be calculated, as well as 95% confidence intervals. Data from Parent 1 and Parent 2 will be compared using paired-samples sign tests in order to determine if there were any differences in the median values of their observations.

When the assumption of homogeneity of regression is not met, transformations will be performed on pre-intervention data. Moreover, Little’s test [46] will be conducted to examine the underlying nature of our missing data. If missing data are missing completely at random (MCAR), a Last Observation Carried Forward (LOCF) framework will be used.

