### 2.7. Sample Size

Sample size calculation was based on the CONSORT 2010 statement extended to feasibility trials [35] and the Lewis et al. [36] methodology. This approach calculates sample size by conducting hypothesis testing based on estimations of predefined feasibility outcomes being within the unacceptable “red zone” (null hypothesis) and contrasting this with an alternative hypothesis of being within the “favorable” green zone [35]. A sample size is considered appropriate if it allows for ≥80% power to reject being in the red zone if the green zone holds true. For detailed information about this methodology, please consult Lewis et al. [36].

Progression parameters and their subsequent point estimates as described in Table 2 were used. Considering a one-tailed, one-sample binomial test based on normal approximation (with continuity correction) with α = 0.05, the following minimum sample sizes for each parameter were obtained:Feasibility of participant retention at post-intervention (Rul = 0.50 and Gll = 0.70)—41 participantsFeasibility of consent rate (Rul = 0.40 and Gll = 0.60)—42 participantsFeasibility of program completion (Rul = 0.45 and Gll = 0.75)—18 participants (intervention arm)Feasibility of program acceptability (Rul = 0.45 and Gll = 0.75)—19 participants (intervention arm)Feasibility of program fidelity (Rul = 0.40 and Gll = 0.70)—19 participants (intervention arm)

Therefore, a sample size of 42 participants, with 25 participants in the intervention arm, allows for ≥80% power to reject the null hypothesis for each of the feasibility outcomes. Moreover, this sample size is sufficient for the estimation of effect sizes for a future larger trial, as it allows for the collection of preliminary data needed to calculate reliable effect size estimates and assess the variability in psychological measures.

Regarding our qualitative data, according to the recommendations of Boddy [37] and van Risjnsoever [38], we aim to recruit 10 to 12 participants, as this sample size is often sufficient to achieve data saturation when the aim is to explore shared experiences within a relatively homogeneous group. Moreover, we will closely monitor data saturation during analysis and will adjust the sample size if necessary to ensure robust and meaningful findings.

**Table 2 healthcare-13-00176-t002:** Feasibility progression parameters.

Parameter	Thresholds		Justification

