1. Feasibility of Retention of Families at Post-Intervention *Can a significant number of recruited families be retained until post-intervention?*	GREEN ZONE (Go—Proceed with full RCT)	>70%	Ensuring a substantial post-intervention retention rate is essential to obtain accurate and unbiased post-intervention data Favorable retention rates at the feasibility trial will contribute to estimating the required sample size for a larger RCT Systematic reviews have shown that attrition rates between 9 to 27% can be found in RCTs testing parenting interventions for childhood behavior problems [39] Previous trials of the BaP program reported an average retention rate of 80% [18,19]
	AMBER ZONE (Amend—Proceed with changes)	50–70%	
	RED ZONE (Stop—Do not proceed unless significant changes are made)	<50%	
2. Feasibility of Consent Rate *Is the rate of eligible families who consented and were randomized favorable for a large-scale RCT?*	GREEN ZONE (Go—Proceed with full RCT)	>60%	An adequate consent rate is essential for the feasibility trial to accurately estimate the number of families who need to be reached, in order to achieve the required sample size to obtain significant statistical power in a large-scale RCT. Low consent rates may provide important information regarding issues in recruitment procedures (such as locations of recruitment or information available to interested participants). Previous trials report an average consent rate of 70% [40] Previous trials of parenting interventions in Portugal report consent rates ranging from 63% to 97% [41,42] Previous studies of the BaP program report an average consent rate of 71% [19]
	AMBER ZONE (Amend—Proceed with changes)	40–60%	
	RED ZONE (Stop—Do not proceed unless significant changes are made)	<40%	
3. Feasibility of Program Completion *Can a significant number of participants from the intervention arm complete the BaP program?*	GREEN ZONE (Go—Proceed with full RCT)	>60%	Achieving favorable program completion rates is critical to obtain accurate and unbiased data A systematic review [43] found a mean program completion rate of 80% with a wide variety across studies between 50% and 100% Previous trials of the BaP program have shown an average completion rate of 70% [18,19]
	AMBER ZONE (Amend—Proceed with changes)	30–60%	
	RED ZONE (Stop—Do not proceed unless significant changes are made)	<30%	

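### The sample size rests on a one-sided 5% test of each red limit, but progression is decided on percentage cut-points, so the Table 2 decision does not carry that 5% error rate

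*Protocol article*

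**What the plan says.** Section 2.7 (Sample Size) sets up a hypothesis test. The null is the "feasibility outcomes being within the unacceptable “red zone” (null hypothesis"), the alternative is the green zone, and the criterion is "≥80% power to reject being in the red zone if the green zone holds true". The test is a "one-tailed, one-sample binomial test based on normal approximation (with continuity correction) with α = 0.05". The section gives minimum sizes of 41 (retention), 42 (consent), 18 (completion), 19 (acceptability) and 19 (fidelity). It concludes that 42 participants, 25 of them in the intervention arm, "allows for ≥80% power to reject the null hypothesis for each of the feasibility outcomes".

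Section 2.8.1 (Quantitative Data) gives the feasibility analysis: "Descriptive statistics will be computed to assess feasibility and acceptability". Fidelity is to be a cumulative score over sessions and a percentage of its maximum. The 95% confidence intervals in that section stand beside Cohen's d for the psychological outcomes.

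Section 2.8.3 refers the progression decision to Table 2, where each parameter has three percentage bands. For retention, below 50% is red (Stop), 50–70% is "AMBER ZONE (Amend—Proceed with changes"), and above 70% is green (Go). No test, critical count or confidence limit is attached to any band.

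**The concern.** The article fixes one procedure for sizing and another for deciding. The boundary used for sizing is the red limit, which separates Stop from the two outcomes that allow the programme to continue. At that boundary the decision uses the bare percentage, so sampling error is not allowed for.

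The progression decision is a central product of a feasibility trial. A low-amber retention result could be reported as grounds for an amended full trial, in a study described as having 5% error and at least 80% power, although the data would not exclude a rate in the red zone.

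**Working it through.** **Inputs.** The red and green limits, one-sided α = 0.05 and 80% power come from section 2.7. The bands come from Table 2. The sample sizes are 42 in total and 25 in the intervention arm (section 2.7), or 21 in the arm if 42 are split 1:1 (section 2.1).

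**Step 1: reproduce the plan's sizes.** With p0 the red limit and p1 the green limit:

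n = [(1.645·√(p0(1−p0)) + 0.842·√(p1(1−p1))) / (p1−p0)]², then with continuity correction n′ = (n/4)·[1 + √(1 + 2/(n(p1−p0)))]².

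| Parameter | p0 / p1 | n | n′ | Stated |
|---|---|---|---|---|
| Retention | 0.50 / 0.70 | 36.49 | 41.34 | 41 |
| Consent | 0.40 / 0.60 | 37.10 | 41.95 | 42 |
| Completion | 0.45 / 0.75 | 15.54 | 18.73 | 18 |
| Acceptability | 0.45 / 0.75 | 15.54 | 18.73 | 19 |
| Fidelity | 0.40 / 0.70 | 15.77 | 18.96 | 19 |

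All agree to within one participant, so this is the test used for sizing.

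**Step 2: the two rules for retention, n = 42.**
- Table 2 avoids red when X/42 ≥ 0.50, so X ≥ 21. Green needs X/42 > 0.70, so X ≥ 30 (29/42 = 69.0%).
- The sizing test rejects red when (X/42 − 0.50 − 1/84) / √(0.25/42) ≥ 1.645. At X = 26 the statistic is 1.39; at X = 27 it is 1.70. The minimum count is therefore 27 (64.3%).
- Counts of 21 to 26 are amber without rejecting the red limit. The exact one-sided 95% lower bound is 48.0% at 26/42 and 50.5% at 27/42.

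**Step 3: exact binomial probabilities for retention, n = 42.**

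| True rate | Avoids red, X ≥ 21 | Sizing test rejects red, X ≥ 27 | Green, X ≥ 30 |
|---|---|---|---|
| 50% (red limit) | 0.561 | 0.044 | 0.004 |
| 45% | 0.309 | 0.009 | 0.0005 |
| 40% | 0.122 | 0.001 | <0.0001 |
| 30% | 0.005 | <0.0001 | <0.0001 |
| 70% (green limit) | 0.998 | 0.836 | 0.496 |

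**Step 4: other participant-level parameters.**

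| Parameter, n | Avoids red at red limit: Table 2 | Same: sizing test | Green at red limit | Green at green limit |
|---|---|---|---|---|
| Consent, 42 | 0.533 | 0.038 | 0.003 | 0.467 |
| Acceptability, 25 | 0.457 | 0.044 | 0.002 | 0.561 |
| Completion (30%/60%, Table 2), 25 | 0.488 | 0.044 | 0.0005 | 0.425 |

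With 21 in the arm, the chance of avoiding red at the red limit is 0.488 for acceptability and 0.449 for completion. Consent is measured among eligible families, whose number is not given; at an assumed 70 the chance is 0.545. Fidelity is scored over sessions, so a binomial over participants does not describe it and it is left out.

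**The case against.** - **Where the half comes from.** A reader might infer that any truly red parameter escapes Stop about half the time. The documents do not support that. The 56% applies at exactly 50%, which Table 2 itself places in amber, and the chance falls quickly below it. The limit is still where the test's error rate is set, so the comparison with 5% is fair there as a worst case.
- **The graver error is controlled.** Green needs 30 of 42 for retention, above the critical count of 27, so every green result also rejects red. Misclassified results go to amber, which requires changes, and the red row itself allows progress after significant changes. This stands and limits the consequence.
- **The 80% is not misdescribed.** Section 2.7 defines it as power to reject red. A reader might take it as the chance of Go, but the article does not say so. The most that is warranted is a clarifying sentence.
- **A full analysis plan may apply the test.** It may. The point is confined to what the article states: a descriptive analysis and percentage bands beside a sizing based on a test. The article does not say in words that the observed percentage is compared with the bands, but it gives no other rule.
- **Making the test the decision rule would gut amber.** Sending every non-rejecting amber result to the red row would move 6 of the 9 amber retention counts (21–26 out of 21–29). At a true 60%, red handling would rise from 7% to 66%. This is a fair objection to changing the zones, but not to reporting the test beside them.

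**Conclusion.** The point holds in a limited form. The 5% error rate that supports the sample size belongs to a test that the stated analysis does not apply, and the Table 2 decision does not have it. At the red limit a parameter avoids Stop about half the time (retention 56% at n = 42, against 4.4% with the test), almost always into amber. For retention this falls to about 31% at 5 points below the limit and 12% at 10 points below. False Go at the red limit is under 0.5% for every parameter tabulated at the planned sizes. When the true rate is at the green limit, green is reached about half the time (0.43 to 0.56 across the four parameters).

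These figures assume independent units, a binomial proportion for each parameter and the denominators shown. The retention figures take all 42 as the denominator. The completion figures use the Table 2 limits, which differ from those in section 2.7.

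**What to change.** - **Sections 2.8.1 and 2.8.3.** For each parameter that is a binomial proportion, carry out the one-sided test used for sizing, with its actual denominator (eligible families for consent). State the minimum count in advance, such as 27 of 42 for retention. Report fidelity over sessions, as it is scored.
- **Interval.** Give a one-sided 95% lower bound or, equivalently, a 90% two-sided interval. A two-sided 95% interval would contradict the test: at 27/42 its exact lower limit is 48.0%, below the red limit that the test rejects.
- **Zones.** Keep Table 2. Report an amber result that does not reject the red limit as amber, red not ruled out, and have the progression decision take this into account.
- **Section 2.7.** Add that the 80% is the chance of ruling out red, and that the chance of green when the true rate is at the green limit is about 50%.

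The cost is protocol wording and a few short calculations on data already to be collected, with no added participants. The small downside is that some low-amber results will be reported less favourably.

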### 2.1. Design

This is a two-arm parallel-group feasibility RCT, in which families will be randomly assigned to an intervention arm and a waitlist control arm, with a 1:1 allocation ratio. Parents in the intervention group will participate in the Being a Parent program, while the waitlist control group will not receive any intervention during this phase but will be given the opportunity to participate in the program after post-intervention assessments are conducted. Two outcome assessments will be completed by both arms at baseline and post-intervention, and an additional 6-month follow-up will be conducted only with the intervention arm, as assessing the control group at this stage would not provide accurate control data for comparison since the control group will have been participating in the Being a Parent program. Concurrently, a qualitative process assessment will be performed using semi-structured interviews to thoroughly explore the experience of the families who participated in the Being a Parent program, independently of their designated trial group. Figure 1 summarizes the participant flow throughout the study. As illustrated, parents will be recruited through different channels and will be asked to sign in through our website. If included in the study, participants will complete baseline assessments and proceed to randomization to either an intervention group or a control group. Post-intervention assessments will be completed by both groups, and the intervention group will have an additional 6-month assessment. Qualitative assessments will also be conducted.

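### Under MCAR, carrying the last observation forward puts the baseline score in place of the post-intervention outcome and shrinks any non-zero effect by the missing share when loss is equal; ANCOVA on the observed data would be unbiased

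*Protocol article*

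**What the plan says.** Section 2.1 sets the assessment schedule: "Two outcome assessments will be completed by both arms at baseline and post-intervention". The third time point is not shared, since the same section says that "an additional 6-month follow-up will be conducted only with the intervention arm". Section 2.3.3 repeats this schedule.

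Section 2.8.1 compares the arms by ANCOVA, "taking pre-intervention data into account as a covariate", and adds that "Cohen’s d effect sizes will be calculated, as well as 95% confidence intervals". It adopts an intention-to-treat approach with the stated purpose of "minimizing bias and providing a robust assessment of treatment effects". On missing data it says that "Little’s test [46] will be conducted to examine the underlying nature of our missing data". The rule that follows from that test is: "If missing data are missing completely at random (MCAR), a Last Observation Carried Forward (LOCF) framework will be used".

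Section 2.7 gives the estimates a later use: "this sample size is sufficient for the estimation of effect sizes for a future larger trial".

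**The concern.** The rule is stated outright, so this is not a detail left to another document. Two features of the design make it a poor choice.

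First, the only assessment before post-intervention is baseline. In the between-arm comparison, LOCF therefore sets the outcome equal to the ANCOVA covariate for every parent who does not return the post-intervention survey. That assumes no change in either arm. At the 6-month follow-up, which only the intervention arm has, a post-intervention score could be carried forward instead, but that assessment is not part of the between-arm comparison.

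Second, the trigger points the wrong way. Under MCAR the families with observed outcomes are a random subset of those randomised, so ANCOVA on them is unbiased. The plan takes the one mechanism that needs no repair and applies a method that adds bias, against the stated purpose of its intention-to-treat approach.

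At stake are the between-arm effects, Cohen's d and their intervals, which are meant to inform the planning of a larger trial.

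**Working it through.** **Inputs from the protocol article**
- Assessments shared by both arms: baseline and post-intervention (2.1, 2.3.3).
- Cited attrition in parenting trials: 9% to 27% (Table 2).
- Average retention in earlier trials of the program: 80%, so 20% missing (Table 2).
- Green lower limit for retention: 0.70, so 30% missing (2.7, Table 2).
- Total sample: 42 (2.7). The LOCF sentence has no figure of its own to reproduce. The 42 does reproduce: for the consent rate (0.40 vs 0.60, one-sided 5%, 80% power), n = ((1.645·√0.24 + 0.842·√0.24)/0.20)² = 37.1, and with continuity correction 41.95, so 42.

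**Assumptions, because the protocol gives no values**
- SD 1 at both times; negative values mean improvement.
- True effect delta = -0.50, control-arm change c = -0.20 and baseline–post correlation 0.7, unless stated.
- 21 per arm (1:1 allocation; a 25/17 split gives the same pattern).
- Missingness independent of everything within arm.

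**Algebra**

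Let m1 and m0 be the missing shares in the intervention and control arms. LOCF gives zero change to the missing, so the expected mean change is (1 - m1)(c + delta) in the intervention arm and (1 - m0)c in the control arm. Baseline is balanced by randomisation, so the expected ANCOVA effect is the difference:

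E[LOCF effect] = delta(1 - m1) + c(m0 - m1)

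With equal loss m this is (1 - m)·delta. The correlation and the change over time drop out.

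**Equal loss, delta = -0.50**
- 9%: 0.91 × -0.50 = -0.455
- 20%: 0.80 × -0.50 = -0.40
- 27%: 0.73 × -0.50 = -0.365
- 30%: 0.70 × -0.50 = -0.35

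**Unequal loss**
- 30% intervention, 10% control: -0.35 + (-0.20)(0.10 - 0.30) = -0.35 + 0.04 = -0.31
- 10% intervention, 30% control: -0.45 + (-0.20)(0.30 - 0.10) = -0.45 - 0.04 = -0.49
- No true effect, c = -0.30, 40% intervention, 10% control: 0 + (-0.30)(0.10 - 0.40) = +0.09

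**Equal loss and no true effect:** (1 - m) × 0 = 0, so the difference is not biased.

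**Simulation check** (6,000 to 8,000 runs per setting; post-intervention score on arm and baseline)

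| Missing, intervention / control | LOCF estimate | LOCF coverage of 95% CI | Observed-data ANCOVA estimate | Its coverage |
|---|---|---|---|---|
| 9% / 9% | -0.45 | 95% | -0.50 | 96% |
| 20% / 20% | -0.40 | 92% | -0.50 | 95% |
| 30% / 30% | -0.35 | 88% | -0.50 | 95% |
| 30% / 10% | -0.31 | 85–86% | -0.50 | 95% |
| 10% / 30% | -0.49 | 95% | -0.50 | 95% |

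**Source of the lost coverage.** At 30% loss in both arms, the LOCF model SE averages about 0.20 and the empirical SD of the LOCF estimate is about 0.21. The SE describes the estimator's variability correctly; the interval is centred on the wrong value. With no true effect and 30% loss in both arms, LOCF coverage is about 95%.

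**Effect on planning.** As an illustration, take a simple two-sample calculation at two-sided 5% and 80% power: n per arm = 2(1.96 + 0.84)²/d² ≈ 15.7/d². A true 0.50 needs 63 per arm. Reported as 0.40 it would suggest 99, and as 0.35 it would suggest 129.

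**The case against.** The best defence is practical. LOCF keeps every randomised family in the analysis. At the attrition the protocol expects, the damage is modest beside the sampling error of a trial of 42: at 9% loss coverage is still about 95%, and at 20% about 92%. With equal loss and a true effect of -0.50, LOCF even has a slightly smaller root mean squared error than observed-data ANCOVA (about 0.24 vs 0.25 at 20%, 0.26 vs 0.27 at 30%). The effectiveness aims are exploratory, and none of the five progression criteria in Table 2 uses the ANCOVA or Cohen's d.

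Most of this stands, and it limits the severity. It does not rescue the rule. The small gain in mean squared error comes from pulling the estimate towards zero, and it reverses for a larger effect: at -0.80 and 30% loss it is about 0.32 for LOCF against 0.27. A planning estimate that is known to be shrunken by the missing share is avoidable at almost no cost.

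A reader might infer several stronger things that the documents do not support:
- **That LOCF makes the standard error too small, and that this is why coverage falls.** The SE matches the estimator's sampling variability; the lost coverage is bias.
- **That the estimates would always be wrong in one direction.** With heavier loss in the control arm, the bias nearly vanishes under the assumed change over time. The spurious +0.09 needs 40% vs 10% loss and a control change of -0.30, none of which the protocol gives.
- **That the last observation is always the baseline.** That holds for the comparison between arms, not for the 6-month follow-up of the intervention arm.

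**Conclusion.** The point holds for the between-arm ANCOVA. Under the very condition that triggers it, LOCF replaces an unbiased analysis with one whose expectation is delta(1 - m1) + c(m0 - m1). With equal loss, a non-zero effect shrinks by 9% to 27% over the cited attrition range, 20% at earlier retention and 30% at the green limit. This proportion does not depend on the assumed effect or correlation. The coverage figures and the unequal-loss results do rest on the assumed values shown above.

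A non-significant Little's test with about 42 families is weak evidence for MCAR, but the conclusion does not need this: it holds even if the data are MCAR.

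The consequence is confined to exploratory effect sizes and intervals intended for planning a larger trial. One might infer that the decision to proceed is compromised. It is not, because retention and the other progression parameters are counted directly. The sentence should be changed before analysis, but this is not a defect that undermines the feasibility trial.

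**What to change.** Replace the LOCF sentence in section 2.8.1 with: the between-arm comparison will be an ANCOVA of the post-intervention score on arm and baseline score, including all families with post-intervention data, in the arm as randomised. This is valid under MCAR, and also if missingness depends only on baseline and arm and the model is correct. Little's test may be reported but should not select the method. Multiple imputation using arm and baseline score is an optional sensitivity analysis.

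The cost is a one-sentence change and no new data. Intervals become somewhat wider (SE about 0.27 instead of 0.20 at 30% loss under the assumptions above). With equal loss, the root mean squared error at this sample size is similar or slightly larger for a true effect of -0.50.
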